#### Primary outcome

The primary outcome is adaptive functioning, measured with the Dutch translation of the Vineland Adaptive Behavior Scales - Survey Version (VABS [30]; Dutch Version [31]; measured at T1, T2, and T3), in order to measure the efficacy of the SST in daily life. Adaptive functioning is defined as the performance of daily living activities that are necessary for personal and social functioning of a person [30] and reflects how well children are able to function in daily life. The Vineland measures this competence with three subscales, in the manual called domains: ‘Communication’ , ‘Daily Living Skills’, and ‘Socialization’. It is an open-ended interview with one or both of the parents. Because the SST does not focus on the domains ‘Daily Living Skills’ and ‘Communication’ of the Vineland, only the domain ‘Socialization’ will be used in the analyses.

#### Secondary outcomes parent measures

The Social Skills Rating Scale (SSRS [32]; measured at T1, T2, and T3) is a 38-item standardized parent questionnaire that measures social skills pertaining to home and community settings for children in primary education, completed by the primary caregiver. The subscales included in the analyses are ‘Cooperation’, ‘Assertion’, ‘Responsibility’ and ‘Self-Control’.

The ESTIA - training specific questionnaire (ESTIA-TS; Unpublished manuscript, 2010; measured at T1, T2, and T3) is a 30-item parent-report questionnaire about the specific social skills children learn during the SST. The questionnaire was developed with the aim to investigate change in the specific behaviors as taught in the SST, such as eye contact, recognizing feelings, and apologizing. Parents report on a scale from 0 to 5 how difficult each skill is for their child. They also report on the frequency of each of the skills.

#### Secondary outcome teacher measure

The Teacher version of the Social Skills Rating Scale (SSRS [30]; measured at T1 and T2) has 30-items in three subscales: ‘Cooperation’, ‘Assertion’, and ‘Self-Control’. All three will be included in the analyses.

#### Other measures

Additionally, possible mediators and moderators of treatment outcome will be assessed, e.g. treatment attendance, genetic factors, severity of ASD, intelligence, symptoms of depression, anxiety, attention deficit, hyperactivity, impulsivity, oppositional behaviors, and parental stress.

### Drop-outs

Children in the intervention groups who dropped out after the start of the SST were encouraged to still participate in the assessments. Post-treatment assessment was organized as soon as the child dropped out of treatment, if the drop out was before session 8. For the follow-up assessment the regular schedule has been followed. Children who dropped out after session 8 were invited for the regular post-treatment assessments.

### Sample size calculation

We computed the minimally required sample sizes for two repeated-measures (RM-)ANOVAs on the primary outcome measure VABS, with one between-subject factor (group; 2 levels) and one within-subject factor (time; 2 levels: T3 versus T1); in one test, the SST and care-as-usual groups will be compared and in the other the SST and SST-PTI groups. For each test, we required a power of .99, a significance level of .01, and assumed a correlation between repeated measures of the VABS of .5. Calculations were performed with the program G*Power 3.1.7 [33].

The expected difference between the SST and the care-as-usual group is based on the results of the study into SST of Owens et al. [34], who found a difference between the treated and untreated group of 0.90 SD of the mean VABS outcome. Assuming no effect in the untreated group, the associated effect size f = .4, yielding a minimal sample size of 21 per group. We expect that comparing the two treatment conditions yields lower values of difference. No literature on the comparison of two SST training conditions was available, therefore we defined the difference to detect based on clinical relevance of a difference found. This resulted in a difference between SST and SST-PTI of 0.60 SD of the mean VABS outcome, with associated effect size f = .3, yielding a minimal sample size of 36 per group. Based on our experiences in past research, we presumed a drop-out rate of 10%, implying a minimal sample size of 21/.9 = 24 children in the care-as-usual condition and 36/.9 = 40 in each of the treatment conditions. Because we could include more children in the treatment groups, yielding an even larger power, we aimed 48 in each of the treatment conditions and 24 children in the care-as-usual group (total n = 120).

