### Randomization

The RCT contains three conditions: SST, SST-PTI, and care-as-usual. As soon as 4–6 children in a treatment center had finished the pretreatment assessment, that group was randomized to one of these three conditions. We used a randomized block design with blocks of 5 with a 2-2-1 ratio (2 SST, 2 SST-PTI, 1 CAU). This balanced randomization procedure was used, striving for unbiased comparison groups, but also for comparison groups of about the same size throughout the trial. The training groups were embedded in three treatment locations that have specific characteristics (Accare Groningen; ATN Groningen; Drachten [including ATN and Accare]). Therefore, we stratified the randomization by the three treatment locations. Research assistants logged in to a web-based program, that allocated groups to treatment condition (randomized on group-level in blocks of 5, stratified per treatment location).

During the inclusion period, the recruiting team was blind to the exact details of the randomization process. To conceal the predictability of the randomization process, research assistants not only entered the treatment location, but also information on the sex of the participants and the number of children in each group (4–6). Sex and group size were in fact not weighed in the randomization.

Randomization took place after all measures of the first assessment were completed. Thus, pre-treatment assessments are independent of the participant’s knowledge of treatment condition.

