### Statistical analyses

First, the three groups will be compared with respect to background, age, IQ, and other data in order to assess the comparability between them.

Second, intervention efficacy will be established with hierarchical linear modeling. All data will be analyzed using the intent-to-treat principle. The comparative efficacies of SST, SST-PTI, and care as usual will be investigated with hierarchical linear modeling. The first will test the primary outcome, the socialization domain of the VABS. The other multilevel analyses will be done on each secondary outcome, including 1) parent reported training-specific social skills and 2) more general social skills pertaining to home and community settings, reported by parents and 3) more general social skills pertaining to home and community settings, reported by teacher.

Third, in the completers, the same analyses will be applied, while taking into account possible drop-out and treatment non-adherence. The possible mediators and moderators will be included as explanatory variables into the hierarchical linear models.

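### The only test the article specifies is a T1-to-T3 change contrast; the hierarchical model should say how T1 and the stratifying location enter, since adjusting for T1 could cut the contrast variance by about a quarter at the planned correlation

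*Protocol article*

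**What the plan says.** Three sections of the protocol article bear on this.

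- **Sample size calculation.** Two repeated-measures ANOVAs on the VABS are planned, each "with one between-subject factor (group; 2 levels) and one within-subject factor (time; 2 levels: T3 versus T1". One is to compare SST with care-as-usual, the other SST with SST-PTI. For each, "we required a power of .99, a significance level of .01, and assumed a correlation between repeated measures of the VABS of .5". The results are "the associated effect size f = .4, yielding a minimal sample size of 21 per group" for the first and, for the second, a difference of 0.60 SD "with associated effect size f = .3, yielding a minimal sample size of 36 per group".
- **Randomization.** Groups of 4 to 6 children were allocated as units. On timing: "Randomization took place after all measures of the first assessment were completed". On strata, the locations are said to have characteristics of their own: "Therefore, we stratified the randomization by the three treatment locations".
- **Statistical analyses.** "The comparative efficacies of SST, SST-PTI, and care as usual will be investigated with hierarchical linear modeling", by intention to treat. The section does not say how T1 enters. The explanatory variables it mentions are possible mediators and moderators; location is neither included nor excluded.

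**The concern.** The contrasts, the time point and the significance level appear only in the sample size section, and the test described there is a change-score comparison. A hierarchical model with a separate T1 mean for each arm, and an arm-by-time term for T3 versus T1, would estimate that same contrast.

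In this trial T1 precedes allocation, so the arms can differ at T1 only by chance. A change score subtracts the whole of that chance difference, although at a correlation of .5 only half of it is expected to persist to T3. The excess is noise in the treatment contrast. With few randomized groups (about 5 in care-as-usual, at 24 children and about 5 per group), chance differences at T1 are likely. The Statistical analyses section plans to check that the arms are comparable but does not say that the baseline outcome will be used.

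At stake is precision in a trial whose recruitment has closed. The usual reason to carry a stratification factor into the model also applies: the analysis should reflect the restriction placed on the randomization.

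**Working it through.** **Inputs from the article.** Alpha .01, power .99, correlation rho = .5, f = .4 and .3, two groups, m = 2 times, three locations, target 48/48/24.

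**1. Reproduce the plan's figures.** For the within-between interaction, lambda = f² · N · m / (1 − rho), with 1 and N − 2 degrees of freedom.

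- f = .4, N = 42: lambda = 0.16 × 42 × 2 / 0.5 = 26.88; power .9915. This gives 21 per group, as stated.
- f = .3, N = 72: lambda = 0.09 × 72 × 2 / 0.5 = 25.92; power .9916. This gives 36 per group, as stated.
- Drop-out: 21/.9 gives 24 and 36/.9 = 40, as stated.

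The between-groups form of the test would need 59 and 102 per group. The sized test is therefore the group-by-time interaction, which is the change-score contrast.

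**2. Variance of the T3 contrast, per child.** In units of the outcome variance, taken as equal at T1 and T3:

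- change score: 2(1 − rho) = 2 × 0.5 = 1.00
- common T1 mean, or T1 as covariate: 1 − rho² = 1 − 0.25 = 0.75
- the gap is (1 − rho)² = 0.25, the part due to chance T1 differences
- ratio: (1 − rho²) / [2(1 − rho)] = (1 + rho)/2

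| rho | ratio | variance saved |
|---|---|---|
| .3 | .65 | 35% |
| .5 | .75 | 25% |
| .7 | .85 | 15% |
| .8 | .90 | 10% |

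At .5 the standard error falls to √.75 = .866 of its value, equivalent to 1/.75 = 1.33 times as many children.

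**3. Effect at the plan's own f.** The minimum size falls from 21 to 16 per group and from 36 to 27. At the stated sizes, power rises from about .99 to about .999 in both comparisons.

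**4. Location.** The article gives no variance between locations. If location explains nothing and costs two degrees of freedom, the minimum sizes are 17 and 27, against 16 and 27 without it. In a simulation with individual allocation (43 vs 43 and 43 vs 22 children, location assumed to carry 0, 2 or 5% of the variance), the variance ratio with T1 as covariate was 0.74 to 0.78. Adding location changed it by less than 0.002. The whole of the quarter comes from T1.

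**5. Clustering.** At about 5 children per group, 120/5 = 24 groups (20 to 30 for group sizes 6 to 4). Steps 2 to 4 treat children as independent. Under group allocation the saving depends on the intraclass correlation and on T1–T3 correlations within and between groups, none of which is given.

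**The case against.** The strongest reply is that the ANOVA is only a device for sizing the trial, and that the efficacy analysis is hierarchical modeling. Sizing on a simple test and analysing with a richer model is common, and a condensed article may leave model terms to a fuller document. This stands in part. A reader might infer that the actual model leaves T1 free and omits location, but the article says neither. What it does show is that the one test it specifies is the less efficient choice and that its two sections are not aligned.

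Other stronger readings also fail:

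- **That the test is biased or invalid.** With T1 measured before allocation, the change contrast is unbiased over randomizations. Chance imbalance adds variance, and the 25% already counts it; it is not a further harm.
- **That the location term contributes to the quarter.** It does not, and no gain from it can be computed from the article.
- **That power is well below .99 for this reason.** If 0.90 and 0.60 SD are read as differences in change, with about 10% drop-out and no clustering, power is .78 rising to .90 with T1 adjustment (43 vs 22) and .56 rising to .72 (43 vs 43). The low starting values come from how the SD differences were converted to f, which is a separate question. At the plan's own f, power is already .99.
- **That T2, or SST-PTI versus care-as-usual, must be demoted.** Nothing about the handling of T1 implies this.

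**Conclusion.** The point holds as an inexpensive improvement, not as an error that invalidates the planned test. Using T1 as a common mean or covariate would reduce the variance of the T3 contrast by 25% at the plan's rho of .5, and by 15% or 10% if rho is .7 or .8. This rests on equal variances at T1 and T3 and on independent children. The size of the gain under group randomization cannot be determined from the article. Location belongs in the model because it stratified the randomization, with no quantified gain claimed for it.

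**What to change.** In the Statistical analyses section, state that the hierarchical model for each outcome

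- uses a T1 mean common to all arms, or T1 as a covariate;
- includes the three-level treatment location as a fixed effect; and
- for the primary outcome, supplies the T3 contrasts for SST versus care-as-usual and SST-PTI versus SST, so that the analysis matches the comparisons that were sized.

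All the variables are already collected. The Trial status section says that the last T3 measurements were still to come, so the wording could be settled before the data are complete. The cost is the wording and two degrees of freedom for location, which matters slightly with about 24 randomized groups.

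### The effect sizes f = .4 and f = .3 do not correspond to the stated 0.90 SD and 0.60 SD, so the stated power of .99 is reached neither at the minimal group sizes nor at the planned 48/48/24

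*Protocol article*

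**What the plan says.** The section on sample size calculation in the protocol article plans two repeated-measures ANOVAs on the VABS, each "with one between-subject factor (group; 2 levels) and one within-subject factor (time; 2 levels: T3 versus T1"). One compares SST with care-as-usual, the other SST with SST-PTI. The inputs are common to both: "we required a power of .99, a significance level of .01, and assumed a correlation between repeated measures of the VABS of .5". The tool is named: "Calculations were performed with the program G*Power 3.1.7".

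For SST versus care-as-usual, the target comes from a published SST study that "found a difference between the treated and untreated group of 0.90 SD of the mean VABS outcome". The section goes on: "Assuming no effect in the untreated group, the associated effect size f = .4, yielding a minimal sample size of 21 per group". For the other comparison the target was set on clinical relevance: "This resulted in a difference between SST and SST-PTI of 0.60 SD of the mean VABS outcome, with associated effect size f = .3", with 36 per group.

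Allowing 10% drop-out, the section raises these to 24 in care-as-usual and 40 in each treatment arm. It then aims for 48, 48 and 24 (total 120) and says that the extra children in the treatment arms raise the power further. Under research aims, SST versus care-as-usual is the main aim and SST-PTI versus SST the secondary aim.

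**The concern.** The differences in SD units, the f values, the group sizes and the power are all given in one paragraph, so they can be checked against each other. In a two-group, two-time interaction test the effect size f is not the one used for a simple comparison of two means, and 0.90 SD and 0.60 SD look too small to be .4 and .3 on that scale.

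If the conversion is wrong, the article claims near-certain detection of differences that the design detects much less often. That matters most for SST-PTI versus SST. There the 0.60 SD was chosen as clinically relevant, and a reader who trusts .99 could take a non-significant result as close to ruling it out.

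**Working it through.** **Inputs, all from the sample size section.** Two groups, m = 2 times (T1, T3), alpha = .01, rho = .5; 0.90 SD with f = .4 and 21 per group; 0.60 SD with f = .3 and 36 per group; drop-out 10%; planned 48/48/24.

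**Step 1. Reproduce the plan's sizes.** For G*Power's default within-between interaction, with N the total over both groups, the noncentrality is lambda = f² × N × m / (1 − rho) = 4 f² N, on 1 and N − 2 degrees of freedom.

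| f | per group | lambda | power |
|---|---|---|---|
| .4 | 21 | 4 × .16 × 42 = 26.88 | .9915 |
| .4 | 20 | 4 × .16 × 40 = 25.60 | .9880 |
| .3 | 36 | 4 × .09 × 72 = 25.92 | .9916 |
| .3 | 35 | 4 × .09 × 70 = 25.20 | .9898 |

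So 21 and 36 are the smallest sizes reaching .99. None of the alternatives tried gives them: the SPSS effect-size option gives 78 and 137, the Cohen option 77 and 136, the between-factor test 59 and 102, and alpha .02 gives 19 and 32.

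**Step 2. What f means on that scale.** If one arm does not change and the other changes by d SD, the four cell means are 0, 0, 0, d. Each interaction effect is ± d/4, so f = d/4.

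- f = .4 means d = 4 × .4 = 1.6 SD; f = .3 means d = 4 × .3 = 1.2 SD.
- 0.90 SD means f = .90/4 = .225; 0.60 SD means f = .60/4 = .15.

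Cross-check: the interaction test is the same as a two-sided t test on change scores, whose SD is sqrt(2(1 − rho)) = 1 SD at rho = .5. With d = 1.6 and 21 per group it returns .9915; with d = 1.2 and 36 per group, .9916.

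**Step 3. Power for the stated differences.** The noncentrality of the t test is d / sqrt(1/n1 + 1/n2), at alpha .01.

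| Comparison | n | noncentrality | power |
|---|---|---|---|
| 0.90 SD, minimal size | 21 v 21 | 2.92 | .587 |
| 0.90 SD, planned | 48 v 24 | 3.60 | .826 |
| 0.90 SD, planned less 10% | 43 v 21 or 22 | 3.38 or 3.43 | .762 or .778 |
| 0.60 SD, minimal size | 36 v 36 | 2.55 | .464 |
| 0.60 SD, planned | 48 v 48 | 2.94 | .622 |
| 0.60 SD, planned less 10% | 43 v 43 | 2.78 | .560 |

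The two values for care-as-usual arise because 24 × .9 = 21.6.

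**Step 4. Sizes for .99.** With f = .225 and .15, the default test needs 62 and 136 per group before drop-out.

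**Step 5. Readings that might restore .99.**

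- SD of change or of a single score: identical at rho = .5.
- Higher correlation: 21 per group reaches .99 at rho of about .84, and 36 per group between .86 and .90. The plan states .5.
- Baseline adjustment at rho = .5 multiplies the residual SD by sqrt(1 − .25) = .866. Power at the minimal sizes becomes .74 and .62.

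**The case against.** The strongest reply is that 21 and 36 are minimal sizes and the trial planned more. That stands. A reader might take .59 and .46 as the power of the trial; they belong only to the sizes to which the article attaches .99. A reader might also call both comparisons primary and both close to a coin flip. The research aims make SST-PTI versus SST secondary, and only that contrast (.56-.62) comes near even odds.

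Second, .99 at alpha .01 is an unusually strict target. At alpha .05 the planned sizes give .94 and .83 for the same differences (.92 or .91, and .79, after drop-out). So the documents do not support a claim that the trial is badly underpowered by ordinary standards. The stated figure is still wrong on its stated alpha.

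Third, the statistical analyses section plans hierarchical linear modeling, not the ANOVA that was powered. If that model adjusted for baseline, which the article does not say, planned power at alpha .01 would be about .93 and .78. Randomization of whole groups, described under randomization, would pull the other way. Neither is counted here, and neither gives .99.

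Fourth, the f values may be right for another program option. Under the Cohen option, f = d/2 applies: .45 and .30 lead to the same 62 and 136 per group. It is tempting to say that a two-group rule f = d/2 was used, and unevenly, since .90/2 = .45 and not .4. But the article does not say how f was obtained, and .4 in place of .45 only makes the sample larger. The cause remains conjecture.

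**Conclusion.** The point holds. The stated differences, correlation, alpha, group sizes and power cannot all be true together. With 0.90 SD and 0.60 SD, the power is about .59 and .46 at the minimal sizes. At the planned 48/48/24 it is about .83 for the main aim and .62 for the secondary aim, falling to .76-.78 and .56 after 10% drop-out. Neither comparison reaches .99 even with no drop-out, so the remark that the larger treatment groups raise the power beyond the target is also wrong.

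These figures assume the article's own test (T3 versus T1, two groups), rho = .5, alpha = .01, no change in the comparison arm for 0.90 SD, and 0.60 SD read as a difference in change. They make no allowance for clustering from group randomization. The error lies in the stated power; it does not bias any planned estimate or test.

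**What to change.** Correct the effect-size inputs to f = .225 for 0.90 SD and f = .15 for 0.60 SD on the default G*Power scale, or to the equivalent under another named option, and say which option was used. Replace the .99 claim with the power that the planned 48/48/24 delivers at alpha .01: about .83 and .62, or .76-.78 and .56 after 10% drop-out, noting that group randomization is not allowed for. Delete the clause saying that the larger treatment groups raise the power further.

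The trial status section reports that all participants have been randomized, and no further enrolment is proposed. The only cost is one reworded paragraph with a less favourable stated power.

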### Statistical analyses

First, the three groups will be compared with respect to background, age, IQ, and other data in order to assess the comparability between them.

Second, intervention efficacy will be established with hierarchical linear modeling. All data will be analyzed using the intent-to-treat principle. The comparative efficacies of SST, SST-PTI, and care as usual will be investigated with hierarchical linear modeling. The first will test the primary outcome, the socialization domain of the VABS. The other multilevel analyses will be done on each secondary outcome, including 1) parent reported training-specific social skills and 2) more general social skills pertaining to home and community settings, reported by parents and 3) more general social skills pertaining to home and community settings, reported by teacher.

Third, in the completers, the same analyses will be applied, while taking into account possible drop-out and treatment non-adherence. The possible mediators and moderators will be included as explanatory variables into the hierarchical linear models.

